- no severe comorbid condition with life expectancy of  $\leq 1$  year,
- no active alcohol or drug abuse, or significant psychosocial difficulties (e.g., psychosis, dementia),
- no recent ischemic stroke (within 7 days),
- no severe renal insufficiency (serum creatinine > 2.5 mg/dL or a calculated creatinine clearance < 25 mL/min),
- no ALT or AST > 2X ULN or a Total Bilirubin  $\geq 1.5$ X ULN (unless an alternative causative factor such as Gilbert's syndrome is identified),
- no platelet count  $\leq 100,000/\text{mm}^3$ ,
- no haemoglobin < 9 g/dL,
- no prior exposure to apixaban,
- no women who are pregnant or breastfeeding

For the 3 criteria involving patient laboratory results (renal insufficiency, low platelet count, and low haemoglobin) a patient will be excluded if their last test result in the 90 days prior to the index date meets the exclusion criteria.

**Step 2:** Next we will determine if/when these patients received apixaban or warfarin. Individuals in EHR who have more than one warfarin eligibility period within their record will be able to contribute more than once to the pool of warfarin subjects (with the covariates and person-time contributed unique to the specific eligibility period) as long as they have no past apixaban exposure.

**Step 3:** Having obtained individual level patient data for ARISTOTLE participants from Bristol Myers-Squibb we will then match each ARISTOTLE apixaban participant 1:1 with the closest available apixaban patient record in our EHR pool. We will consider matching on a selection of the following ARISTOTLE baseline characteristics:

- age
- sex
- body mass index
- systolic blood pressure (mmHg)
- history of congestive heart failure or left ventricular systolic dysfunction

[figure not shown]

- hypertension requiring pharmacological treatment
- diabetes mellitus
- prior stroke or TIA or thromboembolism
- smoking status [current smoker, former smoker, or never smoked]
- alcohol consumption [none, low, moderate, heavy]
- renal impairment [severe, moderate, mild, normal based on the CrCL value]
- prior VKA/warfarin use
- concomitant treatment with:
  - anticoagulant/VKA use other than warfarin or apixaban
  - aspirin
  - antiplatelets
  - NSAIDs
  - lipid lowering drug therapy
  - CYP3A4 inhibitors

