We anticipate matching all or the majority of ARISTOTLE apixaban subjects with an EHR patient, giving us a pool of ARISTOTLE-analogous apixaban patients, with similar baseline characteristics as ARISTOTLE subjects at the point of randomisation (n~9,000).

The variables selected as potential matching variables are those known or suspected to influence the likelihood of the outcomes of interest. The exact selection of matching variables will depend on the quality and completeness of the data available and a balance will be struck between the matched sample size and sample balance. Variables may be grouped together to increase the sample size, for example by grouping concomitant medications that increase bleeding risk. Continuous variables may be coarsened by splitting into appropriate categories. A procedure will be employed to facilitate selection of a matched cohort, for example via coarsened exact matching for example by use of the %CEM SAS macro. Coarsened Exact Matching is a nonparametric matching method that has been found to give estimates of casual effects with lower variance and bias for a given sample size compared with other commonly used methods of matching.

Figure 1: Assembly of Matched Trial-analogous Cohort of EHR Patients

[figure not shown]

Step 4: The resulting trial matched sample of EHR apixaban exposed subjects will be matched to the warfarin ARISTOTLE-eligible EHR subjects (Figure 1) using a matching method such as propensity score matching (PSM), or CEM (with the final method selected based upon method giving the optimal sample size versus balance). Where an individual from EHR has multiple warfarin “eligibility periods” that can be matched to an apixaban trial matched subject, the EHR characteristics that will be matched on will be those from the beginning of the specific eligibility period. The covariates for consideration in the matching between EHR treatment arms or construction of a PS model will include the variables listed above used in in step 3 along with additional EHR variables such as data source (CPRD Gold or Aurum), socioeconomic status, and comorbidities. The hazard ratio for the outcomes of interest (listed in section N) will then be calculated. Each apixaban patient from the ARISTOTLE-eligible EHR

[figure not shown]

patients will be matched 1:1 with the warfarin EHR patient with the closest match giving a trial-analogous analysis cohort of ~18,000.

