#### **N. Exposures, Outcomes and Covariates**

The exposures of interest are apixaban, warfarin, rivaroxaban, and dabigatran (any dose for each exposure).

The individual effectiveness outcomes:

- stroke
- systemic embolism
- myocardial infarction
- all cause death

The safety outcome for the study:

- major bleeding (bleeding requiring transfusion, bleeding at a critical site, bleeding requiring attendance at hospital, or fatal bleeding)

For all outcomes we make the assumption that if there is no record of an outcome then the outcome did not occur.

The EHR ARISTOTLE-eligible patients prescribed apixaban will be matched to the ARISTOTLE apixaban patients on the variables listed in section L (step 3 of objective 1), with value taken at baseline (value at time of first dose or latest measurement/data recorded prior to first dose).

When matching between the treatment arms within the EHR cohort of patients the variables to be considered for inclusion in the matching algorithm include those listed in section L used in matching from the EHR treatment arm to the trial patient data in addition to EHR variables such as data source (CPRD Gold or Aurum), socioeconomic status, and comorbidities.

[figure not shown]

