#### **o Censoring**

##### Index date

The index date for the EHR cohort will be the date of the patient's first prescription of apixaban or warfarin (for objectives 1 and 2), or for objective 3 first prescription of apixaban, warfarin, rivaroxaban, or dabigatran on or after the date the patient first met the eligibility criteria for the trial in the treatment period of interest

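### The protocol does not fix one time zero at which eligibility, matching covariates and start of follow-up coincide in both arms

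*Protocol*

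**What the plan says.** Section L, Objective 1, builds the cohort in order. Step 1 selects patients who would have met the ARISTOTLE criteria. Step 2 then looks for treatment: "Next we will determine if/when these patients received apixaban or warfarin".

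Section O (Index date) states, for Objectives 1 and 2: "The index date for the EHR cohort will be the date of the patient's first prescription of apixaban or warfarin". The sentence ends with the link to eligibility: "on or after the date the patient first met the eligibility criteria for the trial in the treatment period of interest".

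Two groups of exclusions in section L carry their own date. Blood pressure is the latest reading in the 6 months before the index date. Renal function, platelets and haemoglobin are the last result in the 90 days before it.

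Step 2 lets a person enter the warfarin pool more than once, "with the covariates and person-time contributed unique to the specific eligibility period". Section L also lets a warfarin period and a later apixaban period of the same person both be used.

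On covariates, Step 4 has a rule for people with more than one warfarin period: "the EHR characteristics that will be matched on will be those from the beginning of the specific eligibility period". Section N, on matching EHR apixaban patients to the trial's apixaban arm, takes baseline as the "value at time of first dose or latest measurement/data recorded prior to first dose".

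**The concern.** A cohort study that emulates a trial needs one moment per record at which the patient is eligible, the covariates are read and follow-up begins. Here the three are tied to different events: the date criteria were first met, the start of an eligibility period or the first dose, and the first prescription.

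Two things follow if the text is programmed as written. First, a patient can be indexed on a day when a diagnosis-based exclusion applies. Second, a warfarin record can be matched on a profile that is out of date at the start of its follow-up, while its apixaban partner's profile is current. Balance tables built on the same values would not show this.

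Objective 1 decides whether the method is carried to the later objectives. Its first criterion is a point estimate between 0.69 and 0.99, so a modest distortion near 1 could change the conclusion. The planned sensitivity analyses do not test the issue. In section Q, one moves the index date earlier for missing first prescriptions, one extends the date of last dose, and one restricts to the linked cohort.

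**Working it through.** The protocol's only size figure for this cohort reproduces and is not in dispute: 2 × about 9,000 = about 18,000. It gives no interval between eligibility and prescription, so the check is mainly a comparison of texts.

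**1. Is eligibility required at the index prescription?** Section O asks for the date criteria were first met, followed by a prescription on the same or a later day. Suppose a patient with AF and hypertension first meets the criteria in 2013, has an intracranial haemorrhage in 2014 and first receives apixaban in 2015. Section O indexes this patient in 2015, although the Step 1 exclusion for bleeding risk applies on that day. Only the blood pressure and three laboratory exclusions name the index date. Those four also create a circle: the index date depends on eligibility, and their part of eligibility depends on the index date.

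**2. Does one first prescription fit the records allowed?** No. A person with several warfarin periods, or with warfarin and then apixaban, needs an index date for each period. Section O gives one per patient.

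**3. To which objectives does the eligibility clause apply?** It follows the wording for Objective 3 and may belong to that objective alone. Objectives 1 and 2 would then have no stated link between eligibility and index date. If it applies to all, it is undefined for Objective 2 patients who never met the trial criteria.

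**4. Are covariates read at the same time in both arms?**

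| Record | Date of covariates | Where stated |
|---|---|---|
| Apixaban | First dose, or latest value before it | Section N, for the match to the trial |
| Warfarin, several periods | Start of the eligibility period | Section L, Step 4 |
| Warfarin, one period | No separate date given | – |

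The term eligibility period is not defined. If it starts at the index prescription, rows one and two agree. If it starts when criteria are met, they need not.

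**5. What could a covariate lag do?** If both dates fall in the study window (1 January 2013 to 31 January 2019, 2,221 days / 365.25 = 6.08 years), the lag *g* lies between 0 and 6.08 years. As an illustration, assume that the stroke hazard rises by a factor *h* of 1.02 to 1.06 per year of age, that every matched warfarin record lags by *g* years, and that apixaban values are current. The HR is then multiplied by *h*^(−*g*):

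| *g* (years) | *h* = 1.02 | *h* = 1.06 |
|---|---|---|
| 0 | 1.000 | 1.000 |
| 0.25 | 0.995 | 0.986 |
| 0.5 | 0.990 | 0.971 |
| 1 | 0.980 | 0.943 |
| 2 | 0.961 | 0.890 |

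With *g* = 1, a true HR of 1.00 would appear as 0.94 to 0.98, inside the acceptance range. If only a share *m* of warfarin records is affected, the multiplier is 1 / (1 − *m* + *m*·*h*^*g*), which lies between 1 and the tabled value. The protocol gives none of *g*, *h* or *m*.

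**The case against.** The strongest reply is that an eligibility period simply means an eligible warfarin treatment period. The term is introduced in the step about when treatment was received. The same sentence ties covariates and person-time to one period, and person-time starts at the index prescription. Section L later speaks of treatment periods in which the patient is trial-eligible. On this reading the covariate dates coincide. The reading is reasonable, but the protocol never states it, and section O treats eligibility and prescription as dates that can differ.

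Other parts of the reply stand:
- The prescription may fall on the day criteria are first met; it need not be later.
- The EHR cohort is defined by an anticoagulant prescription from the outset, and some exclusions (prior apixaban, concomitant aspirin, stroke within 7 days) are by nature judged at treatment start. That does not cover diagnoses such as dementia or a mechanical valve.
- The Step 4 rule covers only people with several warfarin periods, and section N's first-dose rule is written for the match to the trial.

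A reader might infer that the arms will be matched at different times and that the result is biased towards apixaban and into the acceptance range. The documents do not support this. The mismatch is a possible result of an undefined term, not a prescribed rule. Lapsed eligibility can occur in either arm, and the haemorrhage example concerns an apixaban patient.

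A larger figure is also tempting. If a fraction *f* of warfarin records had acquired an unrecorded stroke that multiplies the rate by 3, then *f* = 10% gives 1 / (1 + 0.10 × 2) = 0.83. But *f* has no source, and the formula assumes that no one has a recorded prior stroke. With an assumed 20% prevalence, the result is (1 + 0.20 × 2) / (1 + 0.30 × 2) = 1.4 / 1.6 = 0.875.

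Detailed derivations may be left to an SAP. Here, however, the point is to correct rules that the protocol already states.

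**Conclusion.** The point holds as a fault in the stated rules. Read literally, the index-date rule can admit records that have lost eligibility on a diagnosis-based criterion, and its single first prescription cannot index the repeat periods that section L allows. These two parts do not depend on how eligibility period is read, although the first assumes that the eligibility clause in section O applies to Objective 1.

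The covariate part is conditional. It arises only for people with several warfarin periods, and only if the period begins before the index prescription. If the dates coincide, there is no effect from covariates.

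The documents establish neither the size nor the net direction of any bias. The illustration shows only that, if lags of about a year were common, they could matter for a criterion with its upper limit at 0.99.

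**What to change.** - **Section O, Index date:** define one index date per treatment record, as the first prescription in that treatment period on which all applicable inclusion and exclusion criteria are met on that date. State which criteria apply for each objective.
- **Section L, Step 4:** replace the reference to the start of the eligibility period with the index date of that record.
- **Sections L and N:** take every matching covariate at or before that index date, by the same rule in both arms and for both matching steps.

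The cost is protocol wording, some programming, and the loss of a small number of records that lost eligibility before treatment. It should be settled before matching.

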##### Date of last dose (all objectives)

The date of last dose will be estimated using the subject's date of prescription, number of tablets prescribed, and daily dose. Where there are missing values for the number of tablets prescribed or daily dose suitable values will be used to replace these, for example by substituting with the median or modal value. To allow for stockpiling of tablets and less than 100% adherence we will add 30 days after the apparent end of treatment when deriving date of last dose.

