### Secondary analyses

Secondary outcomes include the key safety outcome of major bleeding (as defined in section N) and the individual outcomes of stroke, systemic embolism, myocardial infarction, and mortality. All secondary outcomes other than major bleeding will use the same analysis approach (primary censoring scheme and regression model) as specified for the primary analysis above. For major bleeding the same regression model as the primary analysis will be used but with the supportive censoring scheme in which patients are censored around the time of last study drug. Within major bleeding results will also be summarised for intracranial, gastrointestinal, and bleeding at other locations. This safety analysis approach will be used for all 3 objectives.

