We expect different adherence in routine clinical practice compared with the trial adherence may explain some of the difference in treatment effect observed between routine clinical care and the trial. Adherence will therefore be estimated in the EHR cohort to enable comparisons with the trial and investigate the extent to which this may have influenced differences in treatment effect. With the EHR data we do not know how many tablets a patient has taken or if a given prescription is filled by a patient. We will estimate the proportion of time covered by prescribing as a proxy measure for adherence; this proxy measure assumes that all prescriptions are filled and that a patient takes all tablets in the prescription. This measure of adherence is not expected to accurately estimate the adherence of a given individual but should give an idea of how adherent a patient is compared with others. Prescribing for AF in the UK is predominantly through GPs meaning prescribing information from other potential sources of treatment should not be missing. However, it is possible that a patient's first prescription may be issued in hospital and treatment prescribed during any periods of hospitalisation will not be recorded in a patient's EHR leading to missing exposure data.

We will calculate the proportion of days covered (PDC) over a patient's time when on prescribed treatment as a measure of adherence. PDC will be estimated using patient prescription data including the total number of tablets prescribed, daily dose, and number of days on treatment (derived date of last dose – index date +1). This method of estimating adherence cannot easily be used for warfarin due to daily dose being poorly recorded in EHR; in a sample of CPRD Gold warfarin prescription records many patients had dose recorded with noninformative text such as “take as directed”. Depending on the quality of the prescription data warfarin adherence may instead be estimated by looking at patient adherence to other long-term daily medications as a proxy for warfarin adherence; the reliability of this measure would then be explored by comparing this proxy measure in the apixaban users with the PDC calculated directly using the apixaban prescription data.

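### Major bleeding is analysed only up to a last-dose date that needs daily dose, which the protocol itself calls poorly recorded for warfarin, so exposure is probably measured less accurately in the warfarin arm

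*Protocol*

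**What the plan says.** Protocol section O, under Secondary analyses, gives major bleeding its rank: "Secondary outcomes include the key safety outcome of major bleeding". It then separates it from the rest: "All secondary outcomes other than major bleeding will use the same analysis approach", whereas bleeding is analysed "but with the supportive censoring scheme in which patients are censored around the time of last study drug". This holds for all three objectives. The Sensitivity analyses subsection runs the second scheme for efficacy outcomes only, so there is no counterpart that puts bleeding under the primary scheme.

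The supportive scheme adds one censoring point to the primary scheme, the derived last date of study drug. Date of last dose (all objectives) gives a single rule for every drug, based on prescription date, number of tablets and daily dose. For missing quantity or dose, "suitable values will be used to replace these, for example by substituting with the median or modal value". Then "we will add 30 days after the apparent end of treatment when deriving date of last dose".

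Under Sensitivity analyses, where adherence is discussed, the protocol says of the proportion-of-days-covered calculation: "This method of estimating adherence cannot easily be used for warfarin due to daily dose being poorly recorded in EHR". It reports that many patients in a sample of CPRD Gold warfarin records had only non-informative dosing text. It offers substitutes for warfarin adherence (other long-term medicines, INR control) but relies on apixaban prescription data directly. It offers no substitute for the warfarin last-dose date.

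Section Q, Missing Prescription Data, plans a sensitivity analysis that replaces the 30 days with 60 or 90. The stated reason is prescribing during hospital stays.

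**The concern.** Two parts of the same section treat the same data differently. For adherence, warfarin daily dose is judged too poor to use. For the end of exposure, it is used, with gaps filled by a typical value. Section F describes warfarin as needing frequent dose adjustment and varying with drugs, diet and genetics. A typical value will therefore be wrong for many patients, in proportion to the ratio of true to imputed dose. Low-dose patients have their supply ended too early and high-dose patients too late.

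For the efficacy outcomes this matters less, because their main analysis does not use the last-dose date. Major bleeding has no such fallback. The tables of time to discontinuation, and the planned check for informative discontinuation, depend on the same derived date, so they cannot expose the error independently.

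A second problem lies in the added days. The On-treatment Population keeps a switcher's data up to the derived last dose of the first drug, and the supportive scheme has no censoring term for a switch. As written, 30 days (60 or 90 in the sensitivity analysis), plus any unused supply, can be spent on a new anticoagulant but charged to the old one. That works against the scheme's stated purpose of keeping only events attributable to the drug taken.

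**Working it through.** The protocol gives no figure to reproduce here: no tablet counts, no dose distribution and no share of missing doses. The dependence can be traced from the text. The sizes below are illustrations on stated assumptions.

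**Step 1: does any bleeding analysis avoid the last-dose date?** Secondary analyses assigns bleeding to the supportive scheme. Sensitivity analyses lists stroke/SE, MI and mortality for the second scheme, not bleeding. Section Q extends the date by 60 or 90 days but still starts from the estimated end of the final prescription. None avoids it.

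**Step 2: error per prescription.** Error in days = tablets / imputed daily tablets − tablets / true daily tablets. Assume 28 to 112 tablets, imputed 1 to 3 a day and true 1 to 4 a day.
- Longest overrun: 112/1 − 112/4 = 112 − 28 = +84 days.
- Largest shortfall: 112/3 − 112/1 = 37.3 − 112 = −74.7 days.
- Supply of 84 tablets, imputed 2, true 1: 42 + 30 = 72 days, short of the true 84. A 60-day extension covers it (102 days).
- Supply of 112 tablets, imputed 3, true 1: 37.3 + 60 = 97.3 days, still short of 112. A 90-day extension covers it (127.3 days).

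**Step 3: how often.** Assume true dose/imputed dose is lognormal with median 1 and CV 40% to 50%, so σ = √ln(1 + CV²) = 0.385 to 0.472. Let L be the true length of supply and g the days added. Assume also that a patient counts as stopped when a gap between prescriptions exceeds g. Then:
- P(false stop) = Φ(ln((L − g)/L)/σ), and zero if g ≥ L.
- P(end date more than 28 days late) = 1 − Φ(ln((L + 28)/L)/σ).
- P(more than 28 days out either way) adds Φ(ln((L − 28)/L)/σ).

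| | L = 56 days | L = 84 days |
|---|---|---|
| False stop, g = 30 | 2.3% to 5.2% | 12.6% to 17.5% |
| False stop, g = 60 | 0% | 0.06% to 0.4% |
| False stop, g = 90 | 0% | 0% |
| End more than 28 days late | 14.6% to 19.5% | 22.8% to 27.1% |
| More than 28 days out either way | 18% to 27% | 37% to 47% |

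The last two rows describe error in the estimated end of supply before any days are added. Extending g removes most false stops but pushes every late end later still.

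**Step 4: what overrun does to the hazard ratio.** Suppose a fraction f of warfarin time counted as on treatment is really off treatment, with bleeding at r times the on-treatment rate, and apixaban is unaffected. The observed warfarin rate is the true rate × (1 − f + f·r), so apparent HR / true HR = 1/(1 − f + f·r).
- f = 2%, r = 0.7: 1/0.994 = 1.006.
- f = 10%, r = 0.5: 1/0.95 = 1.053.
- f = 20%, r = 0.3: 1/0.86 = 1.163.

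False early stopping works differently. It discards warfarin events and time together, and biases the hazard ratio only if bleeding risk changes over follow-up or the stopping is related to risk.

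**The case against.** The case on the other side is substantial, and several parts of it stand.

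- **No gap rule is stated.** The false-stop figures need one, and section Q can be read as anchoring the date to the final prescription. On that reading a patient who keeps receiving prescriptions is never falsely stopped, and dose error touches only the last supply, against up to five years of follow-up. This stands: the text is ambiguous, and the false-stop row above is conditional on the less favourable reading.
- **The 60- and 90-day analysis covers safety.** It nearly removes false stops even on that reading. This also stands. It does not correct overruns, and it never varies the imputed warfarin dose.
- **The imputation is open.** The median and mode are given as examples, so a drug-, strength- or patient-specific value is allowed and may be set in a statistical analysis plan not shown. That could reduce the error. It would not supply information the protocol says is missing.
- **On-treatment safety analysis mirrors ARISTOTLE.** True, and the point is not against on-treatment analysis. It concerns how the end of treatment is derived, and the absence of a second analysis that does not need it.
- **Switch handling is silence rather than an instruction.** Fair, but the population definition and the censoring list as written leave the overlap in.

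A reader might infer that apixaban time is measured without error. The documents do not support that. No completeness figure is given for apixaban dose, imputation applies to every drug, and the added days and unseen hospital prescribing affect both arms.

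**Conclusion.** The concern holds in this form. Every planned major-bleeding hazard ratio, in all three objectives, depends on a last-dose date whose dose input the protocol itself calls poor for warfarin. Warfarin exposure is therefore likely to be measured less accurately than apixaban exposure. The lack of a stated cut at a switch adds a second, avoidable misattribution.

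The size and direction of the effect on the hazard ratio cannot be settled from the document. The range of 0.6% to 16% applies to overrun in the warfarin arm alone, on assumed values of f and r. The date-error percentages rest on assumed dose variation and supply lengths, and the false-stop ones also on an assumed gap rule. They show that the error could matter, not that it will.

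A reader might also infer that the study's main conclusion is at risk. It is not. The primary endpoint, the noninferiority and superiority conclusions and the two criteria for agreement with ARISTOTLE all use the primary censoring scheme. The effect is confined to the safety analysis, the on-treatment efficacy analyses and the discontinuation summaries.

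**What to change.** 1. Add major bleeding under the primary censoring scheme as a stated sensitivity analysis for all three objectives. This gives one bleeding comparison that does not use the last-dose date.
2. Derive the end of exposure by a rule that does not need daily dose, for example last prescription date plus a high percentile of that drug's observed interval between prescriptions. Apply it in the same way to both arms. Use INR test dates only as a check within the warfarin arm, since an end date based on INR for warfarin alone would create a new difference between arms. State whether an interruption between prescriptions ends exposure.
3. End on-treatment time at the first prescription of another anticoagulant, in the main supportive scheme and in the 60- and 90-day versions.

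The cost is protocol or analysis-plan wording and modest programming, with no new data. The percentile is a judgement and should be fixed before outcomes are analysed.
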